##### Subjects between 12 and 18 years of age

Both the subject and his parents (if they are the legal guardians) or legal guardian will receive oral and written information concerning the study. The subject and his parents/legal guardian should be given adequate time to read the information leaflet and an opportunity to ask the investigator any questions.

Following the provision of subject information, written consent will be obtained from the subject and his parents or legal guardian prior to any study-specific (screening) procedure. The subject is not to enter the study if he or his parents/legal guardian have/has not understood the written and verbal information provided and/or if the subject or his parents/legal guardian has not personally signed and dated the consent form. A copy of the subject information leaflet and the signed informed consent will be provided to the subject and his parents/legal guardian and a copy will be retained by the investigator.

#### **5.1.2 Screening of subjects**

Patient selection will in first instance be based upon a search in a coded database, containing DNA diagnostic data of Duchenne patients. Patients will then be approached and asked for consent. Subsequently, they will be screened according to the inclusion and exclusion criteria. Screening will include evaluation of full DNA diagnostic report, an interview and the assessments as described in the schedule of assessment (Appendix 2: Table 4). Those who meet the selection criteria will be allocated a subject number (subject identification code) which, together with his initials, will ensure unambiguous identification throughout the study.

A skin biopsy will be taken during the screening period for isolation of fibroblasts. These fibroblasts will be converted into myogenic cells, which is a routine procedure in the Prosensa laboratory. For most patients the genetic diagnosis has been assessed on DNA level only, and RNA analysis has typically not been performed. To exclude unexpected effects on splicing and to confirm the mutation on RNA level, RNA will be isolated from the converted cells and analyzed by RT-PCR and sequencing. The cells will also be treated with study drug PRO051 to confirm that the anticipated exon 51 skipping can indeed be obtained.

An alternative and exploratory assay for this subject screening on molecular level will be applied in parallel. It is based on confirmation of patient's mutation and PRO051 response on RNA level using peripheral blood mononuclear cells isolated from small volume (4 ml) blood samples. Upon validation in this study, this relatively simple assay may significantly reduce the molecular screening procedure in future clinical studies and/or applications from 4-6 weeks to 1-2 weeks.

Subject identification codes and initials will be recorded on a subject identification code list, which will be kept on file at the study-site.

### **5.1.3      MRI**

At screening, an MRI will be performed to assess the quality of the muscle in which the biopsy is planned. The MRI is to be performed within 6 weeks prior to the first study medication administration. Subjects will be positioned in the MRI with the legs first. This will avoid discomfort of the subject as this position allows the head of the subject to stay outside the MRI tunnel or at the border of the tunnel.

Abnormalities of the muscle will be assessed using T1-weighted MRI as described by Mercuri et al. and are quantified as mild, moderate or severe. The following criteria apply:

- Mild – traces of increased signal intensity in an otherwise preserved muscle
- Moderate – less than 50% of the muscle show increased intensity
- Severe – at least 50% of the muscle shows increased intensity

### **5.1.4      Skin biopsy – *in vitro* dystrophin mRNA**

If not previously already performed, a skin biopsy will be taken at screening to confirm the patient's original DNA diagnosis on RNA level, being a mutation correctable by exon 51 skipping and allowing a positive response to PRO051. The skin biopsy procedure is to be performed at 6 weeks prior to the first study medication administration in order to allow sufficient time to perform the diagnosis on RNA level.

The skin punch biopsy is collected, stored and transported in sterile cell proliferation culture medium at ambient temperature. Transportation of the sample to the Prosensa Laboratory is within 24 hours by courier mail.

For analytical methods refer to Appendix 4.

### **5.1.5      Peripheral blood mononuclear cells (PB-MNC) – *in vitro* dystrophin mRNA (exploratory)**

At the Prosensa laboratory, an alternative and exploratory assay has been developed which may be used as a straightforward and fast method for confirming patient's original DNA diagnosis and positive response to PRO051 on RNA level. This assay applies peripheral blood mononuclear cells instead of differentiated muscle cell (myotube) cultures derived from a skin biopsy.

Whole blood samples (4 ml) will be collected into EDTA tubes at screening and should be stored at room temperature and sent at room temperature to Prosensa Laboratory within 24 hours by courier mail.

For analytical methods refer to Appendix 4.

### **5.1.6      Pre-study diagnostic muscle biopsy**

If a diagnostic muscle biopsy has been performed at any time prior to the signing of the informed consent, the result for presence of dystrophin in fibers will be collected (in % of fibers positive for dystrophin).

## **5.2      Effect parameters during study period**

### **5.2.1      mRNA production, dystrophin expression and PRO051 levels in muscle biopsy**

A muscle biopsy taken from the tibialis anterior muscle will be taken according to a sparse sampling schedule in order to limit the number of biopsies taken per subject. In cohort 1, a muscle biopsy will be taken at visit 1 (screening) and at visit 8 (day 43). In the other cohorts, a muscle biopsy will be taken at visit 8 (day 43) and at visit 10 (day 78).

The biopsy instrument to be employed is a conchotome (a forceps with two sharp-edged jaws). This instrument is suitable for muscle biopsies in children and does not require full anesthesia. The child can drink or eat normally before the procedure.

At the biopsy site 1 g of a local anesthetic cream (EMLA cream, a hydrophilic cream containing 25 mg lidocaine and 25 mg prilocaine per g) will be applied and covered by a plastic plaster to enhance absorption. The cream will be applied one hour prior to the biopsy to assure good penetration of the skin. A sedative may also be given prior to the biopsy.

After removal of the cream the skin is locally anaesthetized by subcutaneous injection of 3-4 ml of lidocaine 1% without epinephrin. The skin above the anterior tibial muscle is cut parallel to the tibial bone over a length of approximately 1.5 cm. Next a similar incision is made in the muscle fascia. The closed bit of the forceps is introduced through these incisions. The bit is opened just below the muscle fascia to allow muscle tissue to enter the bit. The bit is closed thereby cutting a small piece of muscle of approximately 0.4 x 0.4 x 0.4 cm. The closed forceps is removed and the muscle biopsy is immediately frozen in liquid nitrogen-cooled 2-methylbutane and stored at -80°C till shipment.

After sufficient pieces of muscle tissue (2 to 3 pieces of 100 to 200 milligram each) have been collected, the wound is closed using three sterile adhesive strips. After five days the strips can be removed and replaced by a plaster.

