### **1.3.3 Clinical data with PRO051**

Study PRO051-01 assessed the local dystrophin production restoring effect and safety and tolerability of a single intramuscular dose of 0.8 mg PRO051 in Duchenne muscular dystrophy patients. This study showed for the first time efficient restoration of dystrophin expression in muscle of four DMD patients. Each patient showed specific skipping of exon 51 and sarcolemmal dystrophin in 64% to 97% of myofibers. The treatment was well tolerated, most frequently reported adverse events were related to the muscle biopsy rather than to PRO051 administration. Only one adverse event possibly related to study drug administration was recorded, i.e. mild local pain after intramuscular injection.

From this study it was concluded that PRO051 induces dystrophin protein synthesis when applied intramuscularly in DMD patients with suitable mutations. Also, PRO051 is safe and well-tolerated at this dose level and route of administration.

Refer to Investigator Brochure for summary on PRO051 results.

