## 3 Study design

### 3.1 Overall study design

This study has been designed as an open label, multiple dose, escalating dose study. Depending on the MTD level, twelve to eighteen patients will be studied in four groups.

The study flow chart in Figure 3 outlines the dose escalation design of this study. Patients in the first group will receive 0.5 mg/kg, in the second group maximally 2 mg/kg, in the third group maximally 6 mg/kg and in the fourth group maximally 10 mg/kg.

[figure not shown]

Figure 3. Study flow chart with maximum dose levels to be administered.

Patients will receive one dose of PRO051 per week for 5 weeks. Each group will initially consist of 3 patients. Interim safety review for dose escalation will take place after review of all safety data that have been collected from at least up to and including the first three administrations of study medication (i.e. at least up to and including visit 4) for each patient and no prohibitive adverse events have been observed. In case of potentially dose limiting toxicity (DLT) in one of three patients in one group, this group will be expanded to six patients. In case of similar dose limiting toxicity in two or more patients, the inclusion of patients will be stopped at that dose level. Further, it will be decided if inclusion of new subjects should be stopped, or if the study should continue with a new lower dose group, or if the study should continue by expanding the previous group to six subjects. The dose level of the group which has a dose level one step below the group with similar dose limiting toxicity in two or more patients, will be considered the maximum tolerated dose (MTD).

The decision model for discontinuation or modification of dose escalation schedule is shown in Table 2.

Given the limited number of patients affected by DMD correctable by exon 51 skipping, an adaptive design was chosen to ensure that at least at the highest dose levels a reasonable number of patients could be included and that sufficient data on dose limiting toxicities could be collected. Furthermore, it was considered that the safety and tolerability profile warranting further investigations in a larger population could sufficiently be established with these group sizes.

No control group was included due to the limited number of patients available.

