## **8.5 Statistical methods**

### **8.5.1 General statistical methods**

Subjects will be used as their own reference comparing pre- (baseline) and post-treatment.

Descriptive statistics will be used for description of the frequency and nature of the adverse events. The number and frequency of all adverse events and the adverse events considered possibly or probably related to study will be listed by dose, cumulative dose, body system and by coded term. In addition, the number of subjects experiencing an adverse event will be listed by dose, cumulative dose, body system and by coded term.

Quantitative (incl. biochemical, hematology, muscle strength) parameters will be expressed as mean  $\pm$  SD, median, minimum and maximum per visit.

Pharmacokinetics and dose response relations will be evaluated using population and sparse data analysis.

The analyses will be performed according to the Statistical Analyses Plan that will be available before the database is locked. Deviations from the Statistical Analyses Plan will be justified in the study report.

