#### **8.5.5.4      Safety analysis**

- Adverse events (AEs) will be coded and presented using MedDRA. The overall incidence, the incidence of possibly or probably related as well as the incidence of serious adverse events will be summarized per body system in tables. An adverse event that occurred during the study medication period or at follow-up will only be counted as an adverse event if it was either not present at baseline or it was present at baseline but increased in severity during the treatment period.
- Vital Signs (supine blood pressure and heart rate): Descriptive statistics (n, mean, standard deviation, median, minimum, and maximum) will be provided on blood pressure along with heart rate at baseline and all post-dose assessments.
- Hematology, urinalysis and clinical chemistry parameters: Descriptive statistics (n, mean, standard deviation, median, minimum, and maximum) will be provided on values at baseline and all post-dose assessments. Descriptive statistics will be calculated on the change from baseline measurements. Out-of-normal-range values will be indicated for each parameter. The change in out-of-normal-range values after administration and at follow up versus baseline will be summarized by means of shift-tables.
- ECG: Descriptive statistics (frequency, mean, standard deviation, median, minimum, and maximum) on ECG parameters will be provided at baseline and all post-baseline

assessments. Changes from baseline measurements will be calculated and descriptive statistics will be computed. Shift tables will also be provided to indicate changes in ECG parameters over time.

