| MMT                             | x                      |    |                 |                 |                 |                 |                 |      | x              |      |                 |      | x     | x                       |
| Local tolerability              |                        |    | x               | x               | x               | x               | x               | x    |                |      |                 |      |       |                         |
| Adverse events                  | x                      | x  | x               | x               | x               | x               | x               | x    | x              | x    | x               | x    | x     | x                       |
| Concomitant medication          | x                      | x  | x               | x               | x               | x               | x               | x    | x              | x    | x               | x    | x     | x                       |
| Pharmacokinetic sampling        |                        |    | x  | x  | x  | x  | x  | x    | x              | x    | x               | x    | x     | x                       |

1. Visit to be performed if subject stops prematurely (for any reason)
2. All screening assessments are to be completed within 4 weeks prior to the first study medication administration, unless specified otherwise.
3. To be completed prior to any other screening procedure.
4. To be completed within 6 weeks prior to the first study medication administration.
5. To be completed at 6 weeks prior to the first study medication administration.
6. To be performed if a muscle cell or fibroblast culture is not previously established and analyzed at RNA level for presence of DMD gene exon mutation(s) correctable by exon 51 skipping

7. Vital signs include blood pressure, pulse and respiratory rate
8. Cohort 1 only
9. Cohort 1, 2, 3 and 4t
10. Cohort 2, 3 and 4
11. Only if withdrawal is before the two muscle biopsies have been collected
12. Timed tests consist of: 10-meter walk/run, rising from floor, stair climb
13. See Table 5 for the time points

Table 5. Schedule of assessments during each hospitalization (visit 2-6) in study period

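### Cohort 1 has one post-dose biopsy per boy and cohorts 2-4 have two, so the all-event displays by dose can make 0.5 mg/kg look better tolerated with no drug effect

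*Protocol*

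**What the plan says.** Section 5.2.1 gives every boy two biopsies in the study period but places them differently. For the lowest dose: "In cohort 1, a muscle biopsy will be taken at visit 1 (screening) and at visit 8 (day 43"). For the rest: "In the other cohorts, a muscle biopsy will be taken at visit 8 (day 43) and at visit 10 (day 78"). The footnotes to Table 4 in Appendix 2 agree: the screening biopsy is for cohort 1 alone, the day-43 biopsy is for all cohorts, and the day-78 biopsy is for "Cohort 2, 3 and 4". Dosing runs from day 1 to day 29 (section 3.2.1).

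Cohort is dose. Section 3.1 states: "Patients in the first group will receive 0.5 mg/kg, in the second group maximally 2 mg/kg", with 6 and 10 mg/kg as the maxima for groups three and four. It also states: "Each group will initially consist of 3 patients".

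On counting, section 8.5.5.4 addresses events that arise on drug or in later follow-up. Such an event, it states, "will only be counted as an adverse event if it was either not present at baseline or it was present at baseline but increased in" (the sentence goes on to name worsening on treatment). On display, section 8.5.1 lists the number and frequency of all adverse events and adds that "the number of subjects experiencing an adverse event will be listed by dose, cumulative dose, body system and by coded term". Neither section sets biopsy-procedure events apart.

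On how common such events are, section 1.3.3 reports of the previous PRO051 study that "most frequently reported adverse events were related to the muscle biopsy rather than to PRO051 administration".

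**The concern.** The number of biopsies that can produce a counted event is tied to dose by design. A boy at 0.5 mg/kg who has pain or bruising after his screening biopsy has it before any drug. Unless it worsens later, it does not meet the counting rule. A boy at a higher dose who has the same event after his day-78 biopsy has it in follow-up, where it is new relative to baseline and is counted.

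Safety and tolerability at different dose levels is a stated objective (section 2), and there is no control group (section 3.1). A reader will naturally compare the lowest dose with the others in the all-event displays. That comparison contains a difference in procedures that has nothing to do with the drug. The protocol's own account of the previous study suggests that biopsy events may not be a negligible part of the total.

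**Working it through.** The protocol gives no error rate, power or event rate for this point, so there is no figure of its own to reproduce. The only documented quantity is the biopsy count.

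**Step 1. Countable biopsies (from section 5.2.1, Table 4 and the rule in 8.5.5.4).**

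| Cohort | Dose (mg/kg) | Pre-dose | Post-dose | Post-dose total, 3 boys |
|---|---|---|---|---|
| 1 | 0.5 | 1 | 1 (day 43) | 3 |
| 2 | up to 2 | 0 | 2 (days 43, 78) | 6 |
| 3 | up to 6 | 0 | 2 | 6 |
| 4 | up to 10 | 0 | 2 | 6 |

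If every biopsy carries the same expected number of events whatever the dose, expected counted biopsy events per boy stand at 1:2. This holds for any event rate.

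**Step 2. Share of boys with at least one counted biopsy event (illustrative).** Let p be the chance that one biopsy gives a countable event. The documents do not give p. It is assumed equal for all biopsies, independent between biopsies and unaffected by dose. The share is p in cohort 1 and 1 - (1 - p)² in each of cohorts 2-4. For example, at p = 0.5 the second is 1 - 0.5² = 0.75.

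**Step 3. How often three boys against nine would show it (illustrative).** Take X₁ ~ Bin(3, p) for cohort 1 and X₂ ~ Bin(9, 1 - (1 - p)²) for cohorts 2-4 pooled, and compare X₁/3 with X₂/9 by exact enumeration.

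| Assumed p | Cohort 1 | Cohorts 2-4 | Chance cohort 1 looks lower | Chance it looks higher |
|---|---|---|---|---|
| 0.1 | 10% | 19% | 64% | 21% |
| 0.2 | 20% | 36% | 66% | 22% |
| 0.3 | 30% | 51% | 70% | 20% |
| 0.5 | 50% | 75% | 72% | 18% |
| 0.7 | 70% | 91% | 64% | 20% |
| 0.9 | 90% | 99% | 27% | 6% |

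In the remaining cases the two rates tie. The direction is the same for every p tried.

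**Step 4. Same comparison with equal biopsies.** If only the day-43 biopsy, which all cohorts share, is compared, the expected rates are p and p. At p = 0.5 cohort 1 then looks lower 44% of the time and higher 44% of the time, so the imbalance disappears.

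**Step 5. Effect on total event counts (illustrative).** If biopsy events make up a share s of all events in cohorts 2-4, cohort 1's expected total is 1 - s/2 of theirs. For assumed s of 0.2 to 0.6 this is 0.9 to 0.7, that is 10% to 30% lower.

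**The case against.** The strongest reply is that the exclusion of screening events is inferred. Section 8.5.5.4 speaks only of events in the medication period or at follow-up. Section 7.2 records events from consent, Table 4 collects them at visits 1 and 1a, and section 8.5.1 lists all events. If screening-only events were listed under cohort 1, the biopsy counts would be 2 against 2. This stands as a limit on certainty. It does not remove the problem, because half of cohort 1's biopsy events would then be attributed to a dose that had not yet been given. It is also fair that 8.5.5.4 tabulates by body system without naming dose, so the by-dose effect arises from reading it with 8.5.1.

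A second reply is that procedure-event tables belong in the statistical analysis plan. That plan could well deal with this. But the unequal schedule, the counting rule and the by-dose display are all fixed in the protocol, and it is their combination that produces the imbalance.

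A third is that little turns on it. No formal analysis is planned, boys are their own reference, and listings by coded term in 12 to 18 boys let a careful reader recognise procedural events. The minimum escalation review covers data to visit 4 (day 15), before any post-dose biopsy. Procedure-caused events fall under the unrelated category in section 7.2.1.2, so the related-event tables are largely spared, though by an open-label judgement. All of this stands and keeps the point modest.

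Two stronger readings are tempting and should not be drawn. A reader might infer a spurious graded dose trend. Cohorts 2, 3 and 4 have the same schedule, so 2, 6 and 10 mg/kg compare cleanly and there is only one step. A reader might also infer that a drug effect on biopsy-site bleeding, through aPTT, is mixed in. Post-dose biopsies fall 14 and 49 days after the last dose (43 - 29 and 78 - 29). Section 1.3.2 describes the acute effects as transient and following plasma levels, which drop below a tenth of peak within 24 hours. The documents do not support that argument.

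**Conclusion.** The point holds as a bias in the all-event displays at one place: 0.5 mg/kg against the three higher doses. The documented size is 1 against 2 countable biopsies per boy, hence a 1:2 expected ratio of biopsy-procedure events with no drug effect. This rests on reading 8.5.5.4 as leaving out events confined to screening, on equal risk per biopsy, and on both biopsies being done. The percentages in the working are illustrations under assumed rates, not estimates. The only evidence on frequency is qualitative: four boys given a single intramuscular dose in the previous study. That says little about the biopsy share of events after five subcutaneous doses. The point does not call the escalation rule or the related-event tables into question. It is worth correcting because the lowest dose could otherwise be read as better tolerated for a reason unrelated to the drug.

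**What to change.** In sections 8.5.1 and 8.5.5.4:

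1. Flag adverse events caused by the muscle biopsy.
2. Tabulate them separately, per biopsy performed (events over biopsies), with pre-dose and post-dose biopsies shown. Cohort 1's screening events are then reported without being assigned to a dose.
3. Present the by-dose all-event displays both with and without the flagged events, over the full 18 weeks. Showing both avoids hiding information that outright removal would lose.
4. If wanted, add a display limited to first dose up to the day-78 biopsy, as supportive only. As the main comparison it would give up the last six weeks of follow-up (days 78 to 120) of a drug with an expected terminal half-life of about four weeks (section 5.4).

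The cost is small: one procedure-attribution flag and one or two extra tables, with no new visits or procedures. The flag is needed because the unrelated category in section 7.2.1.2 pools procedure with clinical state and concomitant medication, so procedure cause cannot be recovered from it.
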